# **3.0 Study Design**

This study will be conducted in the Clinical Exercise Research Center (CERC) in the Division of Biokinesiology and Physical Therapy on the University of Southern California Health Sciences Campus. In this mechanistic proof-of-concept clinical trial, the effects of a 12-week periodized RT intervention on the brain will be compared to that of an initial control period of equal duration. After baseline testing, participants will be asked to resume normal life for the 12-week control period. After the control period, and before the RT intervention, participants will undergo the same tests performed at baseline. Post-intervention, participants will be tested again (please see study calendar 9.10).

**Study Visit 1:** Interested participants will report to the CERC and read the informed consent with a study investigator. The prospective participant will be given the opportunity to ask any questions they may have about the study. If the potential subject is willing to take part in the study, she/he will sign the informed consent agreeing to participate. She/He will also complete a Physical Activity Readiness Questionnaire (PAR-Q) to ensure she/he is at a baseline fitness level necessary for exercise training, and a Mini-Mental State Examination (MMSE) to screen for cognitive deficits. All potential subjects will have their blood pressure taken during this visit to ensure normal levels. Additional screening will take place, according to the inclusion/exclusion criteria.

**Study Visit 2 (Baseline Testing Part 1):** All participants will undergo the following tests: cognitive testing, quality of life questionnaires, and MRI scans. Approximate time: 2.5 hours

**Study Visit 3 (Baseline Familiarization Day):** Descriptive factors will be measured on all participants. Then they will undergo exercise and testing familiarization. Approximate time: 1.5 hours

**Study Visit 4 (Baseline Testing Part 2):** All participants will undergo the following tests: International Physical Activity Questionnaire (IPAQ), blood pressure, body composition, blood draw, Physical Function tests, Muscle Strength tests, and estimated VO2max tests. Approximate time: 2.5 hours

**Control Period:** Participants will be encouraged to continue normal activities of daily living and eating routines.

**Study Visit 5 (Pre-Intervention Testing Part 1):** All participants will undergo the following tests: cognitive testing, quality of life questionnaires, and MRI scans. Approximate time: 2.5 hours

**Study Visit 6 (Pre-Intervention Testing Part 2):** All participants will undergo the following tests: International Physical Activity Questionnaire (IPAQ), blood pressure, body composition, blood draw, Physical Function tests, Muscle Strength tests, and estimated VO2max tests. Approximate time: 2.5 hours

**Intervention Period:** The RT intervention will consist of 36 sessions. Participants will perform all sessions at the CERC (3 days per week for 12 weeks), supervised by an exercise specialist. A two-week buffer period will be allowed for participants to make-up missed sessions (up to 6 session, 3 per week).

**Study Visit 7 (Post-Intervention Testing Part 1):** All participants will undergo the following tests: cognitive testing, quality of life questionnaires, and MRI scans. Approximate time: 2.5 hours

**Study Visit 8 (Post-Intervention Testing Part 2):** All participants will undergo the following tests: International Physical Activity Questionnaire (IPAQ), blood pressure, body composition, blood draw, Physical Function tests, Muscle Strength tests, and estimated VO2max tests. Approximate time: 2.5 hours

# **4.0 Device Information**

## **4.1 Magnetic Resonance Imaging (MRI):**

A 3T MRI scanner (Siemens, Malvern, PA) will be used to measure brain morphology (e.g. volume, cortical thickness, hippocampal subfields, and white matter structure and lesions), resting state brain activity, and cerebrovascular function (arterial spin labeling, ASL). Participants will be positioned supine in the MRI scanner with head and neck support and earplugs for approximately 1 hour. An MRI scan is a non-invasive, painless radiology technique that has the advantage of avoiding x-ray radiation exposure. There are no known side effects of an MRI scan. All scanning sessions will have a minimum of two trained personnel with their credentials approved by the Center for Image Acquisition (CIA). MRI safety policies and procedures are described on the CIA website: <http://cia.ini.usc.edu/home/policy_safety>.

# **5.0 Selection and Withdrawal of Participants**

Method of subject identification and recruitment: 23 healthy older adults, age 60-80yrs, will be recruited from the local communities surrounding the USC Health Sciences Campus. They will be assigned a subject identification number (PID) after signing of the informed consent. Recruitment strategies, as well as plans for recruitment to replace potential dropouts during the course of the study, will include flyer distribution (e.g., around the Health Sciences Campus) and, whenever possible, discussion of the study protocol via personal solicitation. The USC Health Sciences Campus is approximately 5 miles from residential areas/business areas, which provide access to health clubs, country clubs, and local gyms, allowing for recruitment of the required number of participants. Only investigators and staff will approach the participants, introduce themselves (stating their name and association with USC and the Clinical Exercise Research Center), discuss the study briefly with the participant (including the time requirements, training protocols, and blood draws), inquire about possible interest on the part of the participant, and, if the participant is interested, obtain a contact number for follow-up. Patients who are not competent to give informed consent will not be recruited.

Potential participants will be given an opportunity to ask questions and seek additional information about the study and alternatives. They will be encouraged to take the informed consent home to read over and discuss with relatives, friends, physician, etc. If they subsequently desire additional information about the study, they will be invited to return for the opportunity to ask more questions. Participants will not be included in the study unless the informed consent is obtained from the participants themselves. The participant will be asked if she/he understands the information in the informed consent and relate that back to the investigator(s).

Documentation of consent: [name], CSCS

E. [name]

Privileges/certificates and licenses: [name] is an Associate Professor in the Division of Biokinesiology & Physical Therapy with a joint appointment in the Department of Medicine. [name] is an Exercise Physiologist, instructor of Clinical Exercise Physiology in the Division of Biokinesiology and Physical Therapy, and director of the Clinical Exercise Research Center (CHP 149). [name] is a doctoral student in the Division of Biokinesiology and Physical Therapy.

Eligibility waivers are not permitted. Patients must meet all of the inclusion and exclusion criteria to be registered to the study. Study treatment may not begin until a subject is registered.

## **5.1 Inclusion Criteria**

The patient must give written informed consent to enter into the study after receiving a full explanation of the study's purpose, procedures, and risks. A copy of the consent form for this protocol will be given to each subject entering the study. All of the following criteria must be met for the subject to be eligible for the study:

- 60-80 year old men and women.
- Community-dwelling and living independently (without need of assistance).
- Interest and availability for participation in a 12-week planned RT program at the CERC, including pre- and post- testing.
- Competency in English sufficient for assessment and training.
- Able to see and hear sufficiently to participate in RT.
- Not engaged in any structured exercise training outside of this intervention.
- Eligible to undergo MRI.
- Answer NO to all questions on the Physical Activity Readiness Questionnaire (PAR-Q) or receive medical clearance from a physician.

## **5.2 Exclusion Criteria**

Patients that meet any of the following criteria are excluded from entry into the study:

- Possible Dementia (score less than or equal to 23 on MMSE).
- History of known neurological disease (e.g. Epilepsy, Multiple sclerosis, Parkinson disease, Alzheimer’s disease), cerebral infarct (e.g. Stroke), or traumatic brain injury.
- History of known cardiovascular or metabolic disease or chronic illness which may compromise the patient’s ability to safely perform the RT program (e.g. coronary artery disease, arrhythmia, asthma requiring an inhaler during exercise), or presently uncontrolled hypertension (SBP > 140 mmHg or DBP > 90 mmHg). Patient may be required to provide clearance from a physician at the study team’s discretion.
- Type 1 or Type 2 Diabetes.
- Changes in chronic pharmacological treatment (e.g. Aspirin, Statins, or ACE inhibitors) or hormone therapy during the intervention period.
- Current treatment for congestive heart failure, angina, uncontrolled arrhythmia, DVT or other cardiovascular event.
- Myocardial infarction, coronary artery bypass grafting, angioplasty or other cardiac condition in the past year.
- Contraindications against MRI (e.g. metal implants, claustrophobia).
- Self-report regular heavy RT in the past 6 months (i.e. “strengthening exercises or lifting weights heavy enough that you could not perform more than 15 repetitions in one set”).
- Musculoskeletal injuries interfering with the ability to perform RT or medical conditions for which exercise in contraindicated.

## **5.3 Withdrawal Criteria**

Patients may be withdrawn from the study due to injury, illness, personal choice, or non-compliance that would prevent participants from completing all visits.

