# **8.0 Assessment of Efficacy and Safety**

Side-effects will be monitored. Participants will be asked about the following side-effects at the beginning of each testing and training session:

- energy level
- muscle fatigue and soreness
- joint stiffness
- pulls/strains
- sleep quality

Other side-effects will be documented if presented by the participant: everyday strength, everyday energy levels, appetite, thirst, sleep quality, or participation in strenuous activity or exercise within 24 hours prior to the visit.

Adverse events will be documented by the PI and the IRB will be notified of any severe adverse events (SAEs) within 24 hours of study team becoming aware of such SAE event. Adverse events (AE) that may be associated with this study include injury or excessive soreness from testing or the resistance training program. No serious adverse events (SAEs) are expected with this study.

No long-term toxicities are to be monitored after completion of the study. No long-term adverse side effects have been associated with resistance training.

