# **9.0 Clinical and Laboratory Evaluations**

Assessments performed exclusively to determine eligibility for this study will be done only after obtaining informed consent. All screening procedures must be performed within 30 days prior to registration unless otherwise stated.

Descriptive factors to be collected include age, height, weight, gender, chronic pharmacological treatment (e.g. ACE inhibitors, Statins, Aspirin), treated pathologies (diabetes, hypertension, high cholesterol, anemia), and hormone therapy status.

Measurements will be conducted over two study visits at each of the following time points for all study outcomes:

1. Weeks 1-2 (Baseline)

2. Week 15 (Pre-intervention)

3. Weeks 28-29, 29-30, or 30-31 (Post-intervention)

Each of these 6 study visits are anticipated to take approximately 2.5 hours. In addition, one familiarization session (~1.5 hours) will be performed during baseline testing.

Buffer Period: In the event a subject in the RT group misses a training session during the 12-week intervention (i.e. has not completed all 36 training sessions by the end of study week 15), she/he will be allowed to complete missed sessions during a 2-week buffer period following the 12-week intervention. A maximum of 6 sessions (3 per week) will be allowed during this period.

All baseline study procedures will be conducted within 2 weeks prior to the start of the intervention, and all post-test study procedures will be conducted within 2 weeks after the end of the intervention (Section 9.10, Study Calendar).

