# **10.0 Criteria for Evaluation and Endpoint Definitions**

The outcome status of all eligible patients will be reported. Endpoint definitions include completion of the resistance training program with at least 80% of the sessions attended and baseline and post-intervention measurements for all variables.

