# **13.0 Statistical Considerations**

## **13.1 Statistical Analysis Plan**

Participant characteristics will be described at baseline. Continuous variables will be examined for normality and described by either means and standard deviations or medians and interquartile range (if not normal); categorical variables will be described with N (%) of each category. Participant characteristics will be compared with missing data and attrition to determine if there are any systematic patterns that should be adjusted for in secondary analyses; any difference with p < 0.25 will be used in secondary analyses to see if there is an effect on the intent-to-treat model.

Comparison of cerebrovascular function (Hypothesis 1) and cognition (Hypothesis 2) between groups will follow intent-to-treat models using longitudinal linear mixed effects modeling to assess the change in these outcomes, with the main factor of period – control versus RT. The stratifying factor of gender will also be included in the model, as is standard. This same modeling will be used to test whether cerebrovascular function mediates the effect of group assignment on cognition by adding cerebrovascular function to the model of cognition and examining the change in the beta coefficient of group (exploratory objective 1). A change in beta coefficient of >20%, will be considered indicative of mediation. Because these data will be preliminary, the primary endpoint will be the effect size calculated from the estimated marginal means of differences in the change by period from the models. This can then be translated more directly into potential clinical effect.

This same modeling technique will be used for outcomes defined in exploratory objective 2. To assess the association of changes in cerebrovascular function and cognition with other outcomes (exploratory objective 3), Spearman correlations of change in outcomes, adjusted for baseline level will be computed for the total group, and stratified by group assignment.

All analyses will be performed with SPSS (v.24).

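### Section 5.3 does not separate stopping RT from leaving the study, which conflicts with the intent-to-treat analysis and can cost the only MRI and cognition measurement made after RT starts

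*Protocol*

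**What the plan says.** - **Protocol 5.3 (Withdrawal Criteria)**, in full: "Patients may be withdrawn from the study due to injury, illness, personal choice, or non-compliance that would prevent participants from completing all visits". The exit is from the study. There is no separate category for someone who stops RT but can still be assessed.
- **Protocol 13.1 (Statistical Analysis Plan):** the comparisons of cerebrovascular function and cognition "will follow intent-to-treat models using longitudinal linear mixed effects modeling to assess the change in these outcomes", with period (control versus RT) as the main factor. Also, "the primary endpoint will be the effect size calculated from the estimated marginal means of differences in the change by period from the models". On attrition: "Participant characteristics will be compared with missing data and attrition to determine if there are any systematic patterns". Differences with p < 0.25 are carried into secondary analyses.
- **Protocol 10.0 (Criteria for Evaluation and Endpoint Definitions):** the outcome status of all eligible patients is to be reported, but the endpoint definitions include "completion of the resistance training program with at least 80% of the sessions attended and baseline and post-intervention measurements for all variables".
- **Protocol 5.0:** recruitment plans include replacing dropouts.
- **Protocol 9.0:** "all post-test study procedures will be conducted within 2 weeks after the end of the intervention". In the calendar (9.10) the post-tests fall in weeks 28-31, after RT in weeks 16-27 and buffer weeks 28-29 where needed.
- **Protocol 3.0:** MRI and cognition are measured at Visits 2, 5 and 7. Strength testing is at the separate Visits 4, 6 and 8. Both post-intervention visits are described as applying to all participants.

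**The concern.** Intent-to-treat needs outcome data from participants regardless of how much training they completed. Section 5.3 allows assessment to end together with training. Section 10.0 ties the endpoint to attendance and complete measurement, and Section 5.0 allows those who leave to be replaced. Together these describe a completer design under an intent-to-treat label.

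The design makes the loss costly. There is one sequence and no concurrent control group. Visit 7 is the only MRI and cognition measurement after RT starts, so a participant withdrawn during RT supplies a control-period change and no observed RT-period change. No comparison arm has similar losses against which to judge the result. The study's main product is the effect size itself, so any selection falls directly on it. A later statistical analysis plan cannot recover a scan that was never taken.

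**Working it through.** **1. What is lost.** The contrast for each participant is (post - pre) - (pre - baseline). Someone withdrawn in weeks 16-27, or in the buffer weeks, has baseline and pre values but no post value. The second bracket is observed and the first is not.

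**2. The plan's own figure.** Section 13.2 gives N = 23, alpha 0.05, power 0.80 and a detectable d of 0.611 for dependent means. For a paired t-test (noncentral t, n - 1 degrees of freedom, noncentrality d x sqrt(n)):
- Two-sided, n = 23: detectable d = 0.6113, and power at d = 0.611 is 0.7996. The stated figure is reproduced.
- One-sided, n = 23: detectable d = 0.535. The stated figure is therefore two-sided and assumes that all 23 are analysed.

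**3. Precision if the planned losses have no post data.** Section 13.2 expects 15% attrition, about 3, which leaves 20.
- Two-sided, n = 20: detectable d = 0.660, and power at d = 0.611 is 0.736.

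**4. Illustration of bias.** Let m of 23 be lost, with effect d0 had they been measured, while the others have d = 0.611. With the SD of the change held the same, the all-participant effect is [(23 - m) x 0.611 + m x d0] / 23.

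| m | assumed d0 | all-participant effect | 0.611 divided by it |
| --- | --- | --- | --- |
| 3 | 0.611 | 0.611 | 1.00 |
| 3 | 0.3 | 0.570 | 1.07 |
| 3 | 0 | 0.611 x 20/23 = 0.531 | 1.15 |
| 3 | -0.3 | 0.492 | 1.24 |
| 1 | 0 | 0.584 | 1.05 |

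At the 5.7% attrition also cited in Section 13.2, 0.057 x 23 = 1.3 are lost. With d0 = 0 the effect is 0.611 x 21.7/23 = 0.576, a ratio of 1.06. The values of d0 are assumptions; the protocol gives none.

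**5. Does modelling the missing values remove the bias?** A simulation assumed three waves with unit SD and common correlation 0.7, an RT effect of 0.5 SD, and 3 of 23 without a post value. The missing post values were predicted from baseline and pre values, as a missing-at-random analysis does.

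| Shortfall in response among those lost | Full data | Missing-at-random estimate |
| --- | --- | --- |
| none | 0.50 | 0.50 |
| 0.5 SD | 0.43 | 0.49 |
| 1.0 SD | 0.37 | 0.50 |

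The full-data column agrees with arithmetic: 0.5 - (3/23) x 0.5 = 0.435 and 0.5 - (3/23) x 1.0 = 0.370. Modelling is unbiased when loss is unrelated to response. Otherwise it does not correct the bias, because the earlier values carry no information about response to RT.

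**The case against.** The strongest opposing case is that Section 5.3 is permissive and loosely worded, and that the analysis already foresees attrition. Much of this stands, and it limits what can be claimed.

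- **A reader might infer that injury or non-compliance automatically removes a participant.** The text says that patients may be withdrawn. The numbered study visits are also distinct from training sessions, so someone who stops RT but can attend testing is not clearly caught. Section 3.0 describes the post-tests as applying to all participants. What remains is that no sentence keeps such a person in assessment, and the decision is left to discretion.
- **A reader might infer that an intent-to-treat estimate is impossible.** It is not. The mixed model keeps the baseline and pre-intervention data and is valid if data are missing at random. Section 13.1 also examines attrition against participant characteristics, and Section 10.0 reports the outcome status of all eligible patients. But about 3 losses give that check little information, and participant characteristics may not capture response to RT.
- **A reader might infer that those lost are the ones who do badly on RT.** The protocol does not show this. Personal choice is also a listed reason, and some who leave would decline assessment under any rule.
- **A reader might infer that harms go unrecorded.** Section 8.0 says "Participants will be asked about the following side-effects at the beginning of each testing and training session", but it also has the principal investigator document adverse events, with 24-hour notice to the IRB for severe ones. The protocol only fails to state follow-up of an event still open when RT stops.
- **The numbers are small.** The figure 0.611 is a minimum detectable effect, not an expected one. The 15% is called conservative, is not confined to the RT period, and the earlier programme reported no dropouts for injury, illness or personal choice. The shift from 0.611 to 0.53 is 0.08, about one third of the standard error of d at n = 20: sqrt(1/20 + 0.611^2/40) = 0.24.

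**Conclusion.** The conflict is real and lies within the protocol. Sections 5.3, 10.0 and 5.0 fit a completer design, while Section 13.1 states intent-to-treat. The consequence is conditional. If loss is unrelated to response to RT, there is no bias, and the cost is precision: with 20 analysed, power at d = 0.611 is about 0.74 and the detectable d about 0.66. If loss depends on response, the estimate is biased and the data cannot reveal it. With 3 of 23 lost, no benefit in those lost and d = 0.611 in the rest, the overstatement is about 15%. That figure rests wholly on these assumptions. In a proof-of-concept study of this size the defect does not invalidate the plan. It is an inexpensive improvement, but it has to be made before participants reach the RT period, because a missed Visit 7 cannot be recovered.

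**What to change.** Divide Section 5.3 into two parts:

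- **(a) Discontinuation of RT.** The participant stays in the study and is invited to Visit 7 and to whichever Visit 8 tests they can do, within the existing post-test window and regardless of sessions completed.
- **(b) Withdrawal from the study.** Used only when the participant withdraws consent to further assessment.

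Then reconcile the related text:

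- **Section 10.0:** the 80% attendance condition defines a secondary completer analysis only.
- **Section 5.0:** replacements may be added, but they do not displace enrolled participants from the analysis.
- **Section 9.0:** state that, for someone who stops RT early, the post-test window is the one in the study calendar.
- **Section 8.0 (optional):** adverse events open when RT stops are recorded up to the post-test contact.

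No rule on when RT itself should stop is proposed.

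The cost is protocol wording, a matching consent sentence, and about one to three participants returning for visits already in the calendar. Some will refuse, so the assumption about missing data is reduced rather than removed. The estimated effect may be slightly smaller.
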